## Abstract

**Supplementary Information:**

The online version contains supplementary material available at 10.1186/s40352-023-00249-2.

## Background

There is increasing interest in the use of police drug diversion (PDD) schemes. Following the review by Stevens et al. (2022), we define such schemes as alternatives to criminalisation for minor drug-related offences, including—but not limited to—simple possession for personal use. They are alternatives that provide people suspected of such offences with an educative or therapeutic intervention, rather than being processed through prosecution and conviction. Such diversion has a long history in English policing, going back at least to the 1930s,^1^ but its use for drug offences was not openly acknowledged until more recently. Several police forces in the UK and elsewhere are now operating such schemes (Shaw et al., 2022; Stevens et al., 2022). Their use is likely to expand as the government drives policy on ‘out-of-court disposals’ (OOCDs), as signalled in the White Paper on a *Smarter Approach to Sentencing* (MoJ, 2020) and by the subsequent Police, Crime, Sentencing and Courts Act 2022. OOCDs include a range of disposals available for use by the police in England and Wales which enable police officers to resolve cases without suspects being charged or prosecuted, of which PDD is one form (Shaw et al., 2022).

There have been randomised trials of some such schemes—including Turning Point in the West Midlands and Checkpoint in Durham—for their effects in reducing offending, with generally positive results (Neyroud, 2018; Weir et al., 2021, 2022). Less is known about the contexts and mechanisms of such programmes in the UK, and about their effects on outcomes other than offending—particularly health outcomes. People who use drugs are highly vulnerable to a range of health harms, not only from overdose, but also from chronic health conditions (Lewer et al., 2021). PDD schemes offer the opportunity to divert people towards drug treatment services that are effective in treating substance use disorders and preventing death (Ma et al., 2019; Stevens et al., 2022). To develop useful knowledge on the contexts, mechanisms, moderators and outcomes of PDD, we decided to carry out a realist evaluation of PDD schemes in England (Pawson & Tilley, 1998). Realist evaluation enables us to move beyond analysing what works in PDD to consider what works, for whom, in what circumstances and why. The work has been co-designed with our policing partners and with User Voice, a charity led by people with lived experience of adverse contact with criminal justice agencies. It is funded by the Cabinet Office Evaluation Accelerator Fund, which aims to build the evidence base on priority policy areas with a view to informing future government spending reviews.

We will focus on the process, outcomes, cost consequences, and equity effects of PDD schemes in Durham, Thames Valley and the West Midlands. Our process evaluation will include a specific focus on the experiences of drug-involved suspects who are exposed to PDD schemes, whether they take up the diversion opportunities or not, as well as the police officers/staff and partner agencies who implement PDD schemes. In assessing outcomes, we will use data already collected by the police, NHS, and drug treatment services to assess the impacts of PDD on crime, hospitalisations and engagement with drug treatment. We will also examine how equitable the effects of PDD are (e.g. by ethnicity and gender). We will use existing realist frameworks such as EMMIE (Johnson et al., 2015), VICTORE (Cooper et al., 2020), and Carroll et al.’s (2007) conceptual framework for implementation fidelity. EMMIE highlights the Effect, Mechanisms, Moderators, Implementation and Economics of particular interventions or families of programmes (Johnson et al., 2015). VICTORE is a complementary but more detailed, realist framework which sensitises us to examine Volition, Implementation, Contexts, Time, Outcomes, Rivalry and Emergence (Cooper et al., 2020). Carroll et al’s (2007) framework is also complementary. It includes examination of four aspects each of adherence to the plans for the intervention (content, coverage, frequency, duration) and moderators of fidelity (intervention complexity, facilitation strategies, quality of delivery, participant responsiveness), plus the identification of essential components of the intervention.

Our analysis is split into six work packages which will produce a realist synthesis (Jagosh, 2019; Pawson, 2002) and a final, revised programme theory by the end of the project in spring 2025. In the remainder of this protocol, we report on the setting and content of the evaluated PDD schemes, and the methods adopted for each of the work packages of our evaluation. In creating this protocol, we have used the items of the RAMESES II reporting standards for realist evaluation (Welch & Tricco, 2016; Wong et al., 2016), although we have made some changes to their order (e.g. the programme theory appears in the section on work package 1) and we report methods separately for each work package. We will also use these standards for reporting results, including main findings, and consideration of strengths, weaknesses and future directions.

## The evaluated PDD schemes

In collaboration with local stakeholders and based on Hoffmann et al.’s (2014) template for intervention description and replication (TIDieR) checklist, we have developed manuals which describe the operation of each of the PDD schemes in the three focus areas: Durham (Hendrie et al. (2023a), Thames Valley (Hendrie et al. (2023b) and the West Midlands (Hendrie et al. (2023c). Their common features are that they involve police contact with people who use drugs who are suspected of committing an offence (e.g. drug possession). We refer to this target group as ‘drug-involved suspects’. In each area, PDD involves diversion to group or individual sessions of drug education and advice instead of proceeding with prosecution for the suspected offence. People who are diverted may also be referred to other services (e.g. local drug treatment agencies) if needed. There are some differences between the three focus areas. In the West Midlands and Thames Valley, the interventions to which people are diverted are provided by third sector organisations and people generally receive online or face-to-face drug education sessions. Eligibility in these areas is confined to people suspected of simple drug possession (with no intent to supply). In Durham, the eligibility criteria include a wider range of offences. Here, the diversion takes the form of one-to-one meetings with staff employed by the police (known as ‘navigators’). These similarities and differences will be studied in our evaluation to examine the various mechanisms and outcomes which they trigger.

The overall study design is a mixed methods realist evaluation which combines a: qualitative assessment of the implementation, contexts, mechanisms, moderators and outcomes of the evaluated PDD schemes; with a quantitative, quasi-experimental analysis of administrative data on the effects of being exposed to the presence of PDD schemes on reoffending and health outcomes. These will be supplemented with analysis of the cost-consequences of the evaluated PDD schemes, an analysis of the equity of their implementation and effects, and a realist synthesis of the various findings from these different methods.

### Work package 1: development of intervention manuals and a theory of change

This part of our work is already complete. It involved running in-person workshops with stakeholders in each of the three focus areas, plus a national stakeholder workshop. Stakeholders included local police officers and managers, and the staff and managers of the agencies which provide the interventions to which drug-involved suspects are diverted, as well as representatives from User Voice and local partner agencies (for example, staff from local NHS liaison and diversion services and public health substance misuse lead officials).^2^ In total, these workshops involved over 70 stakeholders. Prior to the three area workshops, police staff and the agencies that deliver the interventions provided draft descriptions of the PDD schemes based on the TIDieR checklist (Hoffmann et al., 2014), as well as a draft version of the PDD theory of change. The area workshops discussed real life examples of how the schemes operate in practice. In these discussions, we clarified or further adapted the scheme descriptions previously provided. This created more detailed description of the schemes. We also shared vignettes of possible drug possession scenarios, which allowed police officers and other staff to provide operational insight into how they would or would not apply a diversion to a drug-involved suspect.

The revised scheme descriptions for all three focus areas were shared at a national stakeholder meeting. This event provided all stakeholders the opportunity to agree the revised theory of change and their area scheme description.

This theory of change was based on the programme theory provided by Stevens et al.’s (2022) realist review of alternatives to criminalisation for drug possession, with additional input from research published since the search was carried out for this review (in 2018). This additional research was found using similar search terms and databases to those used in the original review. The theory was further developed through discussion with stakeholders at the local and national workshops. The resulting theory of change is available online as a separate document (Stevens et al., 2023). In summary, it suggests that PDD may have positive effects on offending and health outcomes via two causal pathways. One is avoidance of the negative effects of criminalisation. The other is enhancing the support and treatment available to people who are at risk of drug-related offending and health harms. The theory of change also identifies a range of relevant contexts and moderators of the outcomes of PDD, as displayed in Fig. 1.

**Fig. 1 Fig1:**
[figure not shown]
PDD theory of change

The theory of change and the three programme manuals (one each for Durham, Thames Valley and the West Midlands) provide the basis for our adaptive analysis of the process and effects of the three focus PDD schemes, as well as for the assessment of their implementation fidelity.

### Work package 2: process evaluation

Qualitative process evaluations will be undertaken in Durham, Thames Valley and the West Midlands to produce comparable information on the complex processes through which PDD schemes generate outcomes. This work package will investigate: (1) the implementation of PDD schemes; (2) whether and how PDD schemes produce change in drug-involved suspects; (3) the impact of contexts and moderators on how PDD schemes work; (4) perceptions of stakeholders (including drug-involved suspects) of multiple outcomes (including effects on reoffending, health, wellbeing, quality of life, stigmatisation, and family relations); and (5) fidelity of implementation of the PDD schemes.

Data will be collected through semi-structured interviews and focus groups with practitioners and drug-involved suspects. In total, we plan to do 225 interviews; 75 in each of the case study areas. Sample size will be determined by the achievement of data and inductive thematic saturation (Saunders et al., 2018). Focus groups will take place towards the end of the fieldwork period to discuss preliminary findings from interviews.

The inclusion criteria for practitioners is that research participants are involved in the strategy, management and/or delivery of PDD in Durham, Thames Valley or the West Midlands. Police participants will include senior officers in relevant leadership roles (e.g. on drugs and OOCDs), staff from the office of the Police and Crime Commissioner, managers of diversion schemes, and frontline officers. Purposive sampling will be used to recruit frontline officers from a range of roles (e.g. CID, response and neighbourhood teams) and policing districts, as well as to account for variables such as gender, ethnicity and length of service. Interviews will also be carried out with staff from the organisations that deliver the diversion programmes and other support services to which people who are diverted are referred (e.g. drug treatment, housing and employment).

Research participants who are drug-involved suspects will include: service users who were eligible for diversion, have been diverted, and are fully or partially participating in PDD schemes; and people who were eligible for diversion but were not diverted or are not participating. Interviews with drug-involved suspects will be carried out by User Voice’s peer researchers. Interviewees will be selected purposively to inform us on a range of experiences, according to gender, ethnicity, age, type of drug use (e.g. infrequent/frequent cannabis use, infrequent/frequent cocaine use, dependent use of heroin), and engagement in the diversion scheme (none/partial/full).

We will also gather aggregate police force level data for our three focus areas on the numbers of people who: are contacted as drug-involved suspects; are diverted to PDD schemes; participate in such schemes; complete the scheme; receive an OOCD; or receive some form of criminal justice sanction (e.g. caution, charge, sentence). We will ask for these data to be provided for each year from three years before the start of each PDD scheme to March 2024, and broken down by age group, gender and ethnicity. This will inform our analysis of implementation fidelity, as well as our equity assessment in work package 5.

Interviews and focus groups will be transcribed and anonymised and imported into Nvivo software for computer-assisted qualitative data analysis (Dalkin et al., 2021). We will also include memos on our descriptive analysis of the aggregate data in the qualitative dataset. Following adaptive theory (Layder, 1998), provisional codes for the analysis have been derived from our refined theory of change (see Fig. 1) and the conceptual frameworks we drew from EMMIE (Johnson et al., 2015), VICTORE (Cooper et al., 2020) and Carroll et al. (2007). Through a hybrid process of deductive and inductive reasoning and close reading of interview and focus group transcripts, as well as ‘attached memos’ (Dalkin et al., 2021), we will develop a final set of core and satellite thematic codes. These will form the basis for writing up findings on the contexts, mechanisms, moderators and outcomes of the three PDD schemes, and our analysis of the fidelity of implementation.

### Work package 3: quantitative outcome assessment

A quantitative outcome assessment will test hypotheses that the presence of PDD schemes in police force areas reduce adverse health and offending outcomes for drug-involved suspects. The analysis will involve comparing outcomes for cohorts of drug-involved suspects eligible for diversion in our three focus areas (i.e. police forces with PDD schemes), with those for cohorts of similar individuals in three comparison areas (i.e. forces without PDD schemes) that are in groups of police forces that are most comparable to the intervention forces (HMICFRS, 2023).

Participants in our quantitative analysis will be individuals who had contact with the police in relation to illicit drugs, who may have been eligible for diversion (regardless of whether diversion was available, offered or taken up by that individual). Each PDD and comparison police force will identify individuals who had contact with the police for a qualifying offence between 1 October and 2021 and 30 September 2022 and were aged at least 18 years. Qualifying offences will be (a) simple possession of any controlled drug (personal use), and (b) any of: shoplifting, assault, criminal damage, criminal damage without intent to commit, possession of drugs, drunk and disorderly, drunk and incapable, any theft (other than burglary); in combination with a suspected or proven offence in contravention of the Misuse of Drugs Act 1971 or the Psychoactive Substances Act 2016, in the preceding 3 years, OR a flag in police records for involvement with illicit drugs.

We will use two primary outcomes for health and reoffending:

Health—the count of hospital episodes (including unplanned/emergency inpatient admissions and emergency department visits) during the follow-up period that are related to drugs, alcohol, or accidents.Reoffending—a count of how many offences participants commit in the follow-up period, as recorded in the PNC and adjusted for the time that each participant was in the follow-up period.

We will also use the following secondary outcomes:

Health—the measures will be (a) any entry into structured treatment for drug or alcohol use in a community setting during the follow-up period; and (b) retention in treatment for at least 28 days for those who start drug or alcohol treatment.Reoffending—(a) a dichotomous measure of any offending, with analysis offset by the duration of follow-up, and (b) a measure of the total social cost of these crimes, calculated using the costs attributed to each type of crime according to Home Office estimates of the social costs of each type of crime (Heeks et al., 2018).

The data for the quantitative impact assessment will be compiled using individual-level data linkage between databases of administrative records. Participating police forces will share lists of eligible individuals with the Department of Health and Social Care (DHSC), which is a partner in the project. The DHSC will link the data to four national health and criminal justice databases, and then pseudonymise the data before analysis within a secure data system. The four national databases will be:

The Police National Computer, which will be used to derive a measure of historical offending at study entry, and the primary and secondary reoffending outcomes;The National Drug Treatment Monitoring System, which will be used to measure secondary health outcomes (i.e. entry to and retention in drug and alcohol treatment services);Hospital Episode Statistics, which will be used to measure our primary health outcome (i.e. hospital episodes) (Herbert et al., 2017).The Office for National Statistics mortality database, which we will use to identify participants who die during the follow-up period and are to be excluded from our analysis. Deaths will only be used to censor follow-up and not as an outcome because their relative rarity would result in a lack of statistical power for detecting significant effects.

We plan to use multivariable regression to estimate the effect of PDD on primary and secondary outcomes. Our analysis will control for potential confounders including age, sex/gender, ethnicity, health, previous experience of drug or alcohol treatment, offending history, reason for police contact, date of cohort entry, and the force-level baseline probability of each outcome. Our primary outcomes are count variables, and we will therefore use a mixed negative binomial model offset by the logged duration between the study entry date and the end of follow-up. We plan to use a negative binomial model rather than a Poisson model because we anticipate that both outcomes will be overdispersed, with some participants having high counts.

In our primary analysis, we will compare outcomes for all drug-involved suspects eligible for diversion in our focus areas (regardless of whether they were offered or took up diversion) with those for similar suspects in control areas. This is akin to an ‘intention to treat’ design in an experimental study (Hernán & Robins, 2016).

In our secondary analyses, we will:

Compare outcomes for participants who are diverted with those who are not. This is comparable to a ‘per protocol’ analysis in experimental trials (Hernán & Robins, 2016);Report access to diversion by age, sex, ethnicity, and socioeconomic status (as a complement to work package 5 on equity of effects).Test whether the effectiveness of diversion for each outcome varies by police force (while acknowledging that this analysis will have lower statistical power).

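### One qualifying-offence list for all six forces puts non-possession suspects, whom two of the three schemes do not divert, into a primary cohort described as eligible for diversion

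*Protocol article*

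**What the plan says.** The section on the evaluated PDD schemes separates the three areas. Of Thames Valley and the West Midlands it says: "Eligibility in these areas is confined to people suspected of simple drug possession (with no intent to supply". Of Durham it says: "In Durham, the eligibility criteria include a wider range of offences".

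Work package 3 then sets one cohort definition for the three PDD forces and the three comparison forces: "Each PDD and comparison police force will identify individuals who had contact with the police for a qualifying offence". The list opens with "Qualifying offences will be (a) simple possession of any controlled drug (personal use), and (b) any of: shoplifting, assault, criminal damage" and continues with "drunk and disorderly, drunk and incapable, any theft (other than burglary); in combination with a suspected or proven offence" against the drugs legislation in the previous three years, or a police flag for drug involvement. Nothing limits limb (b) to Durham and its comparison force. Limb (b) also names possession of drugs among its offences.

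The population is described in two ways in the same section. Participants are people "who may have been eligible for diversion (regardless of whether diversion was available, offered or taken up by that individual". For the primary analysis, "we will compare outcomes for all drug-involved suspects eligible for diversion in our focus areas" with those for similar suspects in control areas, and the article likens this to intention to treat.

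The model adjusts for the reason for police contact. Variation of the effect by police force is a secondary analysis, which the authors say has lower power.

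**The concern.** In two of the three PDD forces, a limb (b) suspect held for, say, shoplifting or assault is outside the scheme as the article describes it. Such a person still counts as exposed in the primary comparison. The intention-to-treat analogy properly keeps eligible people who were not offered diversion or did not take it up. It does not extend to people the scheme's own criteria exclude.

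The primary estimate would then average the effect in divertable suspects with whatever effect the scheme has on people it cannot divert. If the latter is small, the estimate is pulled towards no effect.

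Two other analyses inherit the problem. In the diverted versus not-diverted comparison, these suspects could not have been diverted for the qualifying contact, so they enter the not-diverted group. In Work package 5, if the same cohort is the denominator for the share of eligible suspects offered diversion, differences in offence mix between groups could create or mask a disparity.

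The stakes are practical. Under Dissemination, operational guidance on PDD depends on the evaluation showing a positive impact.

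**Working it through.** **Step 1. Set the definitions side by side.**

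| Suspect's offence | Durham scheme | Thames Valley and West Midlands schemes | In the Work package 3 cohort |
|---|---|---|---|
| Simple possession, limb (a) | divertable | divertable | yes, all six forces |
| Possession listed in limb (b) | divertable | divertable if simple possession without intent to supply | yes, all six forces |
| Other limb (b) offence | within the wider range, if the list mirrors Durham's criteria | outside the scheme | yes, all six forces |

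The conflict is confined to the last row in the two possession-only areas, and to the matching suspects in their comparison forces.

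**Step 2. Is there a figure to reproduce?** No. The article gives no sample size, event rate, target effect, cohort size by force or offence mix. What follows is an illustration on assumed inputs.

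**Step 3. Share that cannot be diverted.** Let d be Durham's share of the PDD cohort (assumed 0.10 to 0.33) and p the share of the other two areas' cohorts that is non-possession limb (b) (assumed 0.2 to 0.6). The share outside the schemes is f = (1 − d) × p.

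- Low: 0.67 × 0.2 = 0.134
- High: 0.90 × 0.6 = 0.54

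**Step 4. Dilution.** Assume a rate ratio of 0.85 in divertable suspects, 1 in the others, and equal baseline event rates. Pooled ratio = 0.85 × (1 − f) + f.

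- Low: 0.85 × 0.866 + 0.134 = 0.870
- High: 0.85 × 0.46 + 0.54 = 0.931

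Averaging on the log scale, closer to what an adjusted log-linear model does, gives almost the same: 0.85^0.866 = 0.869 and 0.85^0.46 = 0.928.

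**Step 5. Information.** The gross ratio is (ln 0.85 / ln pooled ratio)².

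- Low: (0.1625 / 0.1391)² = 1.36
- High: (0.1625 / 0.0715)² = 5.17

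This is not yet the comparison with a restricted cohort, because the restriction discards the suspects outside the schemes. Taking information as proportional to the number of suspects, and ignoring variation between forces, multiply by the retained share 1 − f.

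- Low: 1.36 × 0.866 = 1.18
- High: 5.17 × 0.46 = 2.38

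A restricted analysis with 80% power at two-sided 5% has a standardised effect of 1.960 + 0.842 = 2.802. In the mixed cohort this becomes 2.802 / √1.18 = 2.58, or 2.802 / √2.38 = 1.82, which is about 73% or 44% power. The restricted cohort is smaller but more powerful under these assumptions.

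**Step 6. Unequal baseline rates.** If suspects outside the schemes have twice the event rate, their weight is 2f / (1 − f + 2f), which is 0.268 / 1.134 = 0.236 or 1.08 / 1.54 = 0.701. The pooled ratio is then 0.85 × 0.764 + 0.236 = 0.885, or 0.85 × 0.299 + 0.701 = 0.955. A lower event rate in this group would reduce the dilution.

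**Step 7. Do the planned analyses remove it?** Adjusting for the reason for contact deals with confounding by offence type. It leaves a single pooled exposure effect, and the article states no interaction between exposure and eligibility. The by-force test is secondary and does not separate divertable from non-divertable suspects within a force.

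**The case against.** The strongest defence is that the design is deliberately area-level. The stated hypothesis concerns the presence of schemes in force areas, among drug-involved suspects, and Work package 3 admits people "who may have been eligible for diversion (regardless of whether diversion was available, offered or taken up by that individual". One list in every force also guards against differential selection. On this reading, a smaller average effect is a different estimand and not a bias. The point has weight, and it is why the common-list cohort deserves a place. It does not settle the matter. The availability wording fits the comparison forces naturally, and if it is read as deliberate over-inclusion it conflicts with the primary-analysis statement "we will compare outcomes for all drug-involved suspects eligible for diversion in our focus areas".

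Several stronger readings are tempting and are not supported:

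- *Nobody in limb (b) could be diverted in Thames Valley or the West Midlands.* Limb (b) itself names possession: "b) any of: shoplifting, assault, criminal damage, criminal damage without intent to commit, possession of drugs". Only its non-possession suspects are in question.
- *The mixed cohort needs up to about five times the information.* That is the gross ratio, which gives the mixed cohort no credit for its extra suspects. The net range on the same inputs is about 1.2 to 2.4.
- *The effect in suspects outside the schemes is exactly zero.* This is an assumption. People with a drug history or flag may be stopped for possession later in follow-up and diverted then, and this can happen only in a PDD force.

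It can also be said that the article is condensed. A force-specific application of limb (b) may have been intended, and Work package 3 refers elsewhere to forces sharing lists of eligible individuals. But the article does fix the cohort definition, and as written it applies to every force. Finally, the reason for contact is a planned covariate, so a restricted analysis should need no new data. That makes the problem easy to cure but does not remove it.

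**Conclusion.** The concern holds in a limited form. The cohort definition in Work package 3 conflicts with the scheme eligibility for two of the three PDD areas and with the stated primary population. The conflict concerns limb (b) suspects whose offence is not possession.

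The direction of the effect on the estimate is towards a rate ratio of 1, provided the schemes do little for people they cannot divert. The size cannot be obtained from the article. The illustrative range (0.85 becoming 0.87 to 0.93, net penalty about 1.2 to 2.4 times) rests on the assumed true ratio, the assumed Durham share and offence mix, equal baseline rates, no effect in suspects outside the schemes, and information proportional to numbers. Later diversion or spillover would shrink the dilution. A higher event rate in suspects outside the schemes would enlarge it.

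A reader might infer that the planned comparison answers no question the protocol asks. The documents do not support that: it can be read as an area-level effect in a broader group. What it does not match is a primary analysis of suspects eligible for diversion.

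**What to change.** Reconcile the scheme description, the cohort definition and the primary-analysis statement before outcomes are analysed.

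1. Define the primary cohort by what the relevant scheme can divert: limbs (a) and (b) for Durham and its designated comparison force, after checking the list against the Durham manual; possession offences only, including possession cases found under limb (b), for Thames Valley, the West Midlands and their comparison forces.
2. State which comparison force serves which PDD force, and include that grouping in the model. The article says only that three comparison forces come from the most comparable groups; it describes no one-to-one pairing.
3. Keep the full common-list cohort as a secondary analysis, labelled as the area-level effect of a scheme being present.
4. Use the non-possession suspects in the two possession-only areas and their comparison forces as an approximate negative control. A clear difference there would point to confounding between forces. Note that later diversion or spillover could produce a small true effect.
5. Use the same eligibility rule for the denominators in the diverted versus not-diverted comparison and in Work package 5.

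The cost is low. The change filters extracts already requested, using the offence type that the model needs anyway. The downside is a smaller primary cohort.
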